#### Secondary outcome measures for the residents

##### Dementia quality of life Instrument (DQoL)

The DQoL is a reliable instrument to assess dementia patients' quality of life (Brod *et al*. 1999). It is administered in this study to measure the effects of applying the SDM framework on residents' quality of life. It is a 29‐items scale and one global item on overall quality of life. It directly assesses five domains of quality of life: positive affects, negative affects, feelings of belonging, self‐esteem and sense of aesthetics. Items are rated on 5‐point visual scales to facilitate the person with dementia' answers. In this study, given the impaired cognitive functioning of residents, the rating scale will be recoded and patients will answer yes or no to each question.

#### Secondary outcome measures for the family caregivers

##### EuroQOL

The EuroQOL (The EuroQol Group 1990) is used to assess family caregivers' quality of life. EuroQOL is a generic health‐related quality of life measure composed of five domains: mobility, self‐care, usual activities, pain/discomfort, anxiety/depression. It is valid and can be applied in the general population (Brazier *et al*. 1993).

##### Short Sense of Competence Questionnaire (SSCQ)

SSCQ (Vernooij‐Dassen *et al*. 1999) is used to assess the sense of competence of the family caregivers of dementia residents. It is a scale to be used for informal caregivers of older adults diagnosed with dementia. It consists of three domains: satisfaction with the demented person as a recipient of care, satisfaction with one's own performance and consequences of involvement in care for the personal life of the caregiver. It comprises seven items to be rated on a 5‐point scale (from very strongly agree to very strongly disagree). In this study, answers will be dichotomized (Vernooij‐Dassen 1993).

#### Secondary outcome measures for the professional caregivers

##### Job Satisfaction Questionnaire (JSQ)

The JSQ consists of 20 items, scored on a four‐point scale, from mostly negative to mostly positive and it consists of five factors: autonomy, competence, emotion, initiative and relation. High scores indicate high levels of job satisfaction (Orrung Walli *et al*. 2013). The factors have Cronbach's alpha coefficients between 0·74‐0·92 (Sellgren *et al*. 2008).

### Process measures

#### SDM interview process questionnaire

A questionnaire has been developed to measure how residents with dementia have been involved in the SDM process from the formal and informal caregivers' point of views. The questions have been developed by combining and adapting the items of two validated tools used to measure SDM in clinical encounters to be applicable in the nursing home situation (Kriston *et al*. 2010, Melbourne *et al*. 2010). Selection has been made based on the principles that will guide the SDM process with persons with dementia in LTC settings and that focus on: needs identification; options provision; advantages and disadvantages explanation; support to the clients in understanding the information given and in expressing their preferences and wishes; agreement about the final plans to satisfy them. Immediately after the SDM interviews, formal and informal caregivers will be asked to complete it.

#### Process evaluation measures

To explore caregivers' satisfaction with the SDM intervention, questionnaires with closed and open questions will be used. Moreover, data on the adherence rate (operationalized as the proportion of caregivers that actually adopt the intervention in the study), relevance, feasibility and maintenance of the intervention (operationalized as the extent to which the intervention is sustained over time) will be collected.

#### Focus group interviews

Focus group interviews with the involved professional caregivers will take place at the end of the project to collect suggestions, observations and opinions on barriers and facilitators to this practice in LTC settings, also considering and discussing national and setting‐related factors that could have affected the intervention's results, such as the organization of the National Health System, the national attention to the SDM attitude in healthcare settings or the nursing home's inner organization. Measurements related to LTC residents, professional and family caregivers will be performed at baseline and 6 months after the intervention (Table 1).

## Data analysis

Quantitative data will be analyzed using the Statistical Package for Social Science (SPSS). The proportion of residents whose SDM documentation on needs satisfaction has been fulfilled, will be analyzed using the Fischer's exact test. Secondary outcomes, at the level of residents, professional and informal caregivers, will be calculated using parametric and non‐parametric tests, making comparison between and within groups. Descriptive statistics will be used to compare the experimental and control nursing home wards for socio‐demographic characteristics and baseline variables. In each country, the focus group discussions' content will be translated into English. Two independent researchers will code the data by using a constant comparative method (Johnson *et al*. 2012). Each researcher will develop and label categories with appropriate codes outlining the core concepts of the focus group interviews. Then, the codes will be combined in clusters to define the concepts and identify similarities and differences between the interviews (Boeije 2002). Codings will be discussed until consensus will be reached.

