## Aim and objectives

This study has the following primary objectives: (1) to assess the feasibility and acceptability of an SDM framework in care planning to be used both to assess the preferences and (un)met needs of the LTC resident with dementia and his family caregiver and to plan tailored and shared actions based on the assessment outcomes; (2) to investigate how the process of SDM evolves between the resident, professional caregiver and family caregiver; (3) to investigate whether it is acceptable to professionals, residents and families becoming, embedded into the clinical practice of the involved LTC settings in Italy and the Netherlands.

The secondary objectives intend to explore the impact of the SDM framework on:
the dementia residents' quality of lifethe family carers' quality of life and sense of competencethe professional caregivers' job satisfactionthe caregivers' satisfaction with the SDM interventionthe organizational context where it takes place, i.e. barriers and facilitators, as perceived by the professionals.

In particular, we want to determine whether the SDM framework is likely to increase the number of residents' preferences and needs together with the actions taken to satisfy them recorded into their ‘life‐and‐care plans’ and whether it improves the residents' psychosocial well‐being.

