### Subjects and settings

Two nursing home wards in the Netherlands and two nursing home wards in Italy are involved. In each country, one ward will randomly be assigned to the intervention group and the other to the control group. The same number of residents, family caregivers and healthcare professionals will be assessed in both groups and the same tools will be used. In the Netherlands two Dementia Special Care (DSC) units in the same nursing home will be recruited, whereas in Italy two different nursing homes will be enlisted, being similar in numbers of residents admitted, staffing patterns and level of medical and psychosocial care provided, as described in their charters of services. To avoid contamination, in the Netherlands the professionals working in the experimental DSC unit will not be the same as the ones working in the control DSC unit.

In each experimental and control nursing home ward, 20 dementia residents will be included, based on the following inclusion criteria: (1) having a diagnosis of dementia based on DSM IV (American Psychiatric Association 2000); (2) being able to give informed consent or, if legally incapable, having a family caregiver who can give informed consent for them; and (3) being supported by one primary family caregiver who agrees to participate and to be involved in the study too.

Inclusion criteria for the principal professional caregivers are: (1) being a member of the multidisciplinary team who is used to being directly involved in the care planning process; and (2) being a key staff member in the provision of residents' care and consequently to know the identified residents well. In both countries, at least eight healthcare professionals will be recruited to attend the training provided for the project and will later conduct the SDM interviews with 20 residents and their family caregivers.

Thus, the entire experimental group is composed by a total of 40 dementia residents, 40 family carers and about 16 healthcare professionals. These participants will be compared with the two other control nursing home wards that will be asked to involve the same number of subjects. After the selection is completed, a researcher will check the accuracy of the choices based on the requested inclusion criteria.

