#### b) Phase 1 – Training for professionals

Dementia experts with an expertise in teaching communication skills in the context of clinical care have developed a training for professionals, teaching them how to appropriately stimulate the residents with dementia during the SDM interview to facilitate the expression of their wishes and needs. This training will be provided to the professionals in the intervention wards of both LTC settings. The training programme will focus on the SDM principles in dementia care and active listening (Gordon 2000), to enhance the healthcare professionals' verbal and non‐verbal communication skills to be used to assess, meet and record the residents' needs and preferences during the SDM interview. Participants will receive a 2‐hour weekly training for 5 weeks. Each lesson will be guided by clearly defined learning goals and will be divided into three sessions: theory, role‐playing and feedback sessions.
Theory sessionsDuring these sessions, the healthcare professionals will learn the SDM model, active listening and self‐management principles as a guide to: (1) identify residents' problems or needs; (2) prioritize them, choosing the main needs or problems that will become the goals of the intervention; (3) identify alternatives to meet them; (4) decide and plan the intervention; (5) execute plans and (6) evaluate the outcomes.Role‐playing sessionsDuring these sessions, professionals will practice skills and knowledge acquired in the theoretical part of the lesson. In some cases, the trainer will provide case‐vignettes that will be used as cues to set up role‐play exercises; in others professionals will be asked to report difficult situations they face during their daily work. Moreover, professionals will be invited to bring real care plans, to understand whether SDM is applied and to practice the learning objectives of the training programme in daily care situations.Feedback sessionsThe trainer will support and supervise the professionals during the role‐playing sessions, guide the discussion and provide feedbacks to stimulate reflection on their own professional attitude.

One additional lesson, 3 months after the end of the training, will be organized to discuss the problems professionals faced so far and to refresh some of the core issues of the training.

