### Strengths and limitations

The key element of this study is that it will contribute to our knowledge about the efficacy and of SDM interviews in nursing homes with persons with moderate to severe dementia and will consider the barriers and facilitators to this practice in LTC settings. Besides, it will make an important contribution to test the feasibility for a full trial, as recommended by the United Kingdom Medical Research Council guidance on the development and evaluation of complex intervention (Craig *et al*. 2008). Moreover, the study will take place in nursing homes located in two different countries, Italy and the Netherlands: these data represent a source of interesting information on the application and feasibility of this study in countries characterized by different cultures and healthcare systems organization.

At the same time, cultural differences may affect the primary and secondary outcomes: these data are therefore collected and considered during data analysis. Furthermore, only a few nursing homes are recruited in this study: their organization and residents population may not be representative of these parameters in both countries. In addition, the supportive presence of the family caregivers during the SDM interview may influence the resident's behaviour and attitude. Therefore, this co‐variable will be taken into account.

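### Four wards are randomised, but the primary outcome is tested with a resident-level Fisher's exact test, so error control is not assured and the intervention cannot be separated from the ward

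*Protocol article*

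**What the plan says.** Under Subjects and settings, the protocol article states that "Two nursing home wards in the Netherlands and two nursing home wards in Italy are involved". It then says: "In each country, one ward will randomly be assigned to the intervention group and the other to the control group". The number per ward is fixed: "In each experimental and control nursing home ward, 20 dementia residents will be included". The two Dutch wards are units of one nursing home with separate staff, and the two Italian wards are in different nursing homes. The intervention is delivered through ward staff: "This training will be provided to the professionals in the intervention wards of both LTC settings".

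The primary outcome is binary for each resident and is read from the life-and-care plan that the professional caregivers keep up to date. Table 1 lists it by documentation review at baseline (B) and at six months (F1). Under Data analysis, this proportion "will be analyzed using the Fischer's exact test". The only other statement there about wards is a descriptive comparison of their socio-demographic and baseline characteristics. No cluster adjustment, ICC, ward-level analysis or stratification by country is stated for the primary test.

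Strengths and limitations says of the study that "it will contribute to our knowledge about the efficacy and of SDM interviews in nursing homes".

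**The concern.** Fisher's exact test takes its reference distribution from individual residents allocated independently. Here the allocated unit is the ward. Residents of one ward share the staff who interview them and write their plans, and the outcome is what those staff have written. Ward habits in documentation are therefore part of the measurement, and residents of a ward are likely to resemble one another on it.

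Two consequences follow. First, the p-value takes no account of variation between wards, so its nominal error rate is not guaranteed. Second, each country has one ward per arm. Any difference between arms within a country is also a difference between two wards and, in Italy, between two nursing homes. A resident-level test cannot tell these apart. At stake is whether a small p-value on the primary outcome would say anything about shared decision-making, or only that wards document differently.

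**Working it through.** **Inputs from the protocol article (Subjects and settings).** 4 wards; 2 per arm; 1 per arm per country; 20 residents per ward.

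**Stated figure reproduced.** 2 wards x 20 residents = 40 per arm, which agrees with the article's total: "the entire experimental group is composed by a total of 40 dementia residents, 40 family carers and about 16 healthcare professionals". With the same number of controls, 2 x 40 = 80 residents. The article gives no alpha, power, effect size or ICC, so there is no power calculation to reproduce.

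**Assumptions.** Two-sided 5% level; ICC from 0 to 0.20; true proportion equal in all wards on average, at 0.2, 0.3 or 0.5.

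**Step 1, design effect.** DE = 1 + (20 - 1) x ICC = 1 + 19 x ICC. Effective residents per arm = 40 / DE.

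**Step 2, false-positive rate of the planned test.** Simulation of 40,000 trials per setting, with no intervention effect, beta-binomial ward rates, two wards of 20 per arm, and Fisher's exact test on 40 v 40. Ranges are over the three null proportions.

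| Assumed ICC | DE | Effective residents per arm | Rejection rate of nominal 5% test |
|---|---|---|---|
| 0 | 1.00 | 40.0 | 2.7-3.2% |
| 0.01 | 1.19 | 33.6 | 4.4-5.3% |
| 0.02 | 1.38 | 29.0 | 6.1-6.9% |
| 0.05 | 1.95 | 20.5 | 11.6-13.0% |
| 0.10 | 2.90 | 13.8 | 20.1-21.8% |
| 0.20 | 4.80 | 8.3 | 32-35% |

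The simulation draws the four ward rates from one distribution and does not model country pairs. Because each country contributes one ward to each arm, differences between countries balance across arms. The ICC in the table must therefore be read as the correlation due to ward differences within a country.

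**Step 3, what the randomisation itself supports.** Two possible allocations in each of two countries give 2 x 2 = 4. The smallest one-sided p-value is 1/4 = 0.25 and the smallest two-sided p-value is 2/4 = 0.50. A ward-level t-test has 2 degrees of freedom unpaired (critical value 4.30), or 1 if paired by country (critical value 12.71).

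**Step 4, effect on an interval.** Take 60% v 30% as an illustration. With 40 per arm, the standard error = sqrt(0.6 x 0.4/40 + 0.3 x 0.7/40) = sqrt(0.01125) = 0.106, and the 95% half-width = 1.96 x 0.106 = 0.208, or 21 points. The variance is multiplied by DE, so the width is multiplied by sqrt(DE): 20.8 x sqrt(1.95) = 29 points at ICC 0.05, and 20.8 x sqrt(2.90) = 35 points at ICC 0.10.

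**The case against.** The strongest reply is that the size of the problem is not known. With an ICC of about 0.01, Fisher's own conservatism keeps the error near 5%, and inflation becomes material only from about 0.02 to 0.05 upward. The design also limits ward differences within a country: the Dutch wards are in one home, and the Italian homes were chosen as similar in resident numbers, staffing and level of care. The plans have a similar structure in both countries, so plan format is weak evidence of ward differences. All of this stands, and it is why the rates above are conditional on an assumed ICC. A reader might infer that the error rate is certainly inflated by a known amount. The document does not support that.

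Table 1 also records the outcome at baseline, so pre-existing documentation differences will be visible, and the contrast is repeated in two countries. That is useful but partial. A baseline can show where two wards started, but it cannot show whether they would have changed alike without the intervention.

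The study is called a feasibility study, and no significance rule or confidence interval is planned. A reader might infer that a small p-value will be reported as proof of efficacy. The article does not say so: elsewhere it speaks of potential effectiveness, and it concedes that few homes are recruited. The feasibility label lowers the weight of the p-value, but it does not make the named test fit the design. The limitations raised (culture, representativeness, family presence) do not include the confounding of arm with ward.

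Finally, the first primary objective is "to assess the feasibility and acceptability of an SDM framework in care planning", so a reader might infer that the primary endpoint should move to adoption or completion. That is a separate question. The same section also asks whether documentation is likely to increase, and correcting the test does not require a new endpoint.

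**Conclusion.** The point holds as a mismatch between the unit of randomisation and the unit of analysis in the primary outcome's only stated test. The article itself fixes that test, so this is not a detail left to an analysis plan that is not shown.

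Two parts are certain and need no ICC. Arm and ward cannot be separated within either country, and four allocations give no design-based route to a two-sided p-value below 0.50. The third part is conditional: the nominal 5% test is near nominal at a within-country ward ICC of about 0.01, but rejects a true null about one time in eight at 0.05 and one in five at 0.10. Values in that range are plausible for an outcome written by ward staff, but they remain an assumption.

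**What to change.** - In Data analysis, drop the Fisher test as inference on the primary outcome.
- Report the number and proportion of residents meeting the outcome by ward and country, at baseline and at F1.
- Give within-country and pooled risk differences, labelled exploratory.
- If intervals are shown, multiply the variance by 1 + 19 x ICC (the width by its square root) over a stated range such as 0.01 to 0.20. Mark them as illustrative because there are only two wards per arm, and attach no significance claim.
- State in Data analysis and in Strengths and limitations that ward and intervention effects cannot be separated, nor in Italy nursing home and intervention effects.
- Reword the efficacy sentence in Strengths and limitations to match.

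The cost is a few sentences and a few lines of analysis, with no extra residents or wards and no change of primary endpoint. The downside is that the reported effect becomes less certain, which reflects what four wards can show.

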***Professional caregivers***			
*Secondary outcome measure*			
Job satisfaction	Job Satisfaction Questionnaire	C	C
Assessment of the SDM professional attitude	Structured interviews	C	C
*Process measures*			
Assessment of the SDM interview process	Self‐report questionnaire	–	C/FC
Satisfaction with the SDM process; relevance, feasibility and maintenance of the intervention	Self‐report questionnaires	–	R/FC
Barriers/facilitators and influencing factors	Focus group interview	–	C/FC

B, baseline; F1, 6 months after the first SDM interview; P, patient file; C, professional caregiver as informant; I, structured interviews with participants; DR, documentation review; R, residents as informant; FC, family caregiver as informant.

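### Secondary outcomes: within-group and between-group tests are planned without a ranking, and a baseline-adjusted between-group estimate should carry the inference

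*Protocol article*

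**What the plan says.** The Data analysis section of the protocol article says that secondary outcomes, for residents, professionals and informal caregivers, will be analysed with parametric and non-parametric tests, "making comparison between and within groups". It names no model, covariate or deciding comparison for these outcomes. Its one statement on baseline values is that "Descriptive statistics will be used to compare the experimental and control nursing home wards for socio‐demographic characteristics and baseline variables".

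The data would allow more. The timing sentence under Focus group interviews says that "Measurements related to LTC residents, professional and family caregivers will be performed at baseline and 6 months after the intervention". Table 1 uses two columns, defined as "B, baseline; F1, 6 months after the first SDM interview". The DQoL, EuroQOL, sense-of-competence and job satisfaction (JSQ) scales, all labelled secondary outcome measures, have entries in both. The process items do not: the row "Satisfaction with the SDM process; relevance, feasibility and maintenance of the intervention" has no baseline entry.

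Subjects and settings describes a concurrent control. In each country one ward is randomised to intervention and one to control, with the same tools used in both. There are 40 residents, 40 family carers and about 16 professionals in the experimental group, and the control wards are asked for the same numbers.

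**The concern.** Within-group testing is a stated choice here, placed level with the between-group comparison. A before-after test in one arm discards the control that the design provides. Over six months residents with dementia may decline, and carers and staff may change simply because they are assessed. A within-group p-value cannot tell any of this from an effect of SDM. With two sets of tests and no ranking, a report could set a significant change in the intervention arm beside a non-significant one in the control arm and read the contrast as benefit, although no test compared the two changes.

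The second issue is precision. Every one of the four scales has a baseline, and only two wards per arm are randomised, so chance differences between arms at baseline are likely. The article does not say that the baseline score will enter the between-group analysis. The study is meant to inform a full trial, so a misleading or needlessly imprecise signal would carry forward.

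**Working it through.** The article gives no significance level, standard deviation, effect size or sample-size calculation for these outcomes, so there is no planned figure to reproduce.

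**Inputs from the article.** 20 residents × 2 wards = 40 per arm; about 16 professionals per arm; two time points.

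**Assumptions, not in the article.** Two-sided 5% level; baseline-to-follow-up correlation ρ from 0.3 to 0.8; equal drift d in both arms, from 0 to 0.5 SD; independent individuals.

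**1. Within-group tests when SDM has no effect.** For a paired t-test with n per arm, the noncentrality is d√n / √(2(1−ρ)). Let p be the resulting chance of significance in one arm. Exactly one of the two arms is significant with probability 2p(1−p), and only the intervention arm with p(1−p).

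Example, n = 40, ρ = 0.5, d = 0.3: noncentrality 0.3 × 6.325 / 1 = 1.90; p = 0.457; 2 × 0.457 × 0.543 = 0.496; intervention arm only 0.248.

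Probability that exactly one arm is significant, n = 40:

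| Drift (SD) | ρ = 0.3 | ρ = 0.5 | ρ = 0.7 |
|---|---|---|---|
| 0 | 0.095 | 0.095 | 0.095 |
| 0.2 | 0.296 | 0.359 | 0.459 |
| 0.3 | 0.453 | 0.496 | 0.445 |
| 0.4 | 0.495 | 0.425 | 0.196 |
| 0.5 | 0.384 | 0.227 | 0.042 |

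The maximum of 2p(1−p) is 0.50, at p = 0.5. Beyond that point the probability falls again, because both arms become significant. With 16 per arm it also reaches 0.50 (ρ = 0.7, d = 0.4).

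**2. Precision of the between-group estimate.** Relative to a comparison of six-month scores alone (variance 1), a change-score comparison has variance 2(1−ρ) and a baseline-adjusted comparison 1−ρ². The ratio of adjusted to change score is (1−ρ²) / (2(1−ρ)) = (1+ρ)/2.

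| ρ | Change score | Adjusted | Adjusted ÷ change score |
|---|---|---|---|
| 0.3 | 1.40 | 0.91 | 0.65 |
| 0.5 | 1.00 | 0.75 | 0.75 |
| 0.7 | 0.60 | 0.51 | 0.85 |
| 0.8 | 0.40 | 0.36 | 0.90 |

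For scale only, with an assumed true difference of 0.5 SD, power at ρ = 0.5 / 0.7 is:
- 40 per arm: 0.61 for follow-up only, 0.61 / 0.82 for change score, 0.73 / 0.88 adjusted.
- 16 per arm: 0.29 for follow-up only, 0.29 / 0.45 for change score, 0.37 / 0.51 adjusted.

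**3. Limit set by the wards.** With 20 residents per ward the design effect is 1 + 19 × ICC: 1.19 at an assumed ICC of 0.01 and 2.90 at 0.10. The powers above ignore this and are too high in absolute terms. With four wards, a mean, an arm effect and a country effect leave 4 − 3 = 1 degree of freedom between wards. Baseline adjustment does not repair that.

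**The case against.** The strongest reply is that the article does not commit to a poor analysis. A reader might infer that between-group tests will be unadjusted and use six-month scores alone, or that within-group tests will decide. The text says neither. Parametric tests between and within groups at two time points could include change scores or a group-by-time analysis, both of which use baseline. Calling the descriptive ward comparison the sole role of baseline would add a restriction that the article does not state. Nor does it say that significance in one arm and not the other will count as evidence. A condensed article may leave the choice of model to an analysis plan, and Strengths and limitations promises that cultural differences and the family caregiver's presence will be considered. These points stand, although neither promise concerns the baseline score.

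It can also be said that the study is a feasibility trial with exploratory secondary objectives; that 50% is a worst case; that the gain over a change score shrinks as the correlation rises; and that a linear model does not obviously suit a DQoL answered yes or no or dichotomised sense-of-competence items. The first three limit the size of the point. The last is met by modelling the scale score rather than single items.

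None of this removes the within-group testing that the article does state, unranked beside the between-group comparison.

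**Conclusion.** The point holds in a limited form. The plan states within-group tests, does not say that conclusions rest on the between-group comparison, and leaves open whether baseline is used. Within-group tests do not estimate the SDM effect. Under equal drift they disagree between arms in about 10% of trials at zero drift and up to 50% at worst, and at most about 25% of trials show change in the intervention arm only. These figures assume a 5% level, independent individuals and the drift and correlations shown.

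The documents do not support the stronger conclusion that the plan wastes a known amount of precision. The saving depends on an assumed correlation and on the comparison it replaces: at 0.5 to 0.7, the adjusted variance is 75% to 51% of follow-up only and 75% to 85% of a change score. The point covers the four scales with a baseline. It does not cover the process and satisfaction questionnaires, although caregivers' satisfaction is among the secondary objectives.

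**What to change.** In Data analysis, state that for the DQoL, EuroQOL, sense-of-competence scale and JSQ:

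- inference rests on the between-group difference in the scale score at six months, from a linear model with the baseline score of the same scale and country as covariates;
- the result is reported as an exploratory estimate with a confidence interval, with the caveat that two wards per arm cannot separate ward effects from arm effects;
- within-group change is reported descriptively, without p-values.

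Process and satisfaction questionnaires stay outside this rule, since they have no baseline.

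The cost is a sentence or two. No new data are needed, and the model runs in SPSS, the package already planned. If an analysis plan already says this, the article's sentence only needs to be brought into line with it.
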